### Characteristics of participants

For the present study, only subjects who provide written informed consent are eligible. Furthermore, participants should be between 45 and 75 years and should be overweight or slightly obese (body mass index between 25 and 35 kg/m^2^), because these subjects are expected to have increased arterial stiffness and blood pressure at baseline, allowing for improvement by the intervention [19]. To avoid any possible variations in the study outcomes due to hormonal effects, only postmenopausal women (≥ 2 years after last menstruation) will be included. Participants who meet any of the following criteria are not eligible for this study:high magnesium intake (defined as urinary magnesium excretion of ≥ 7.0 or ≥ 5.9 mmol/24 h for men and women, respectively);plasma glucose ≥ 7.0 mmol/l;serum total cholesterol ≥ 8.0 mmol/l;serum triglycerides ≥ 2.2 mmol/l;current smoker or smoking cessation < 12 months;presence of diabetes mellitus;familial hypercholesterolemia;abuse of drugs;more than 21 alcoholic consumptions per week;unstable body weight (weight gain or loss > 3 kg in the past 3 months);use of proton pump inhibitors;use of lipid-lowering drugs and/or antihypertensive therapy that started in the past 6 months;use of magnesium supplements or an investigational product within another biomedical within the previous 1 month;severe medical conditions that might interfere with the study, such as epilepsy, asthma, kidney failure or renal insufficiency, chronic obstructive pulmonary disease, inflammatory bowel diseases, autoinflammatory diseases and rheumatoid arthritis;active cardiovascular disease; ornot willing to give up being a blood donor (or having donated blood) from 8 weeks before the start of the study and during the study.

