### Interventions

The overweight and slightly obese participants will be randomly assigned to receive: magnesium citrate; magnesium oxide; magnesium sulfate; or placebo. A flow chart of the study interventions is presented in Fig. 2. Study participants will be requested to take 2 capsules thrice daily for 24 weeks. On the test days, the first 2 capsules will be taken after all measurements are completed. Each magnesium supplement provides 75 mg magnesium (Magnesium Citrate Complex (Mg 15.5%) Magnesium Sulphate Complex (17.4%) and Magnesium Oxide Complex (60.3%); AMT Laboratories Inc.). Thus, daily magnesium intake provided by the 6 capsules will be 450 mg. The placebo capsules will contain starch (Amylum solani). The total treatment duration of 24 weeks is based on our previous study that showed a significant effect of magnesium supplementation on arterial stiffness after 24 weeks [9]. At baseline and weeks 2, 12 and 24, participants will undergo PWV_c–f_, office blood pressure and body composition measurements. Prior to each test day, participants will collect 24-h urine and fecal samples. In addition, participants will be requested to complete the Patient Health Questionnaire (PHQ-15) before each test day. The PHQ-15 is a somatic symptom subscale derived from the full PHQ. This questionnaire includes about 15 somatic symptoms or symptom clusters that account for more than 90% of the physical complaints reporting in the outpatient setting [20]. Finally, subjects will record any signs of illness in diaries, as well as medication used, and any deviations from the protocol during the study. Subjects are requested not to change their physical activity level, their food intake pattern or use of alcohol during the entire study.

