### Compliance to the intervention

Compliance will be assessed based on the number of returned capsules after 12 and 24 weeks. Subjects will be considered compliant when they take at least 80% of the capsules. In addition, we will assess compliance by urinary magnesium concentrations at the end of the study.

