### Statistical analysis

For normally distributed parameters, data will be presented as the mean value and standard deviation. Nonnormally distributed parameters will be presented as the median (range). For statistical analyses, responses will be calculated defined as the difference between follow-up and baseline values. For the primary analyses, in which the effect of magnesium citrate on arterial stiffness will be evaluated, differences in responses between magnesium citrate and placebo will be tested (one-factor ANCOVA) with use of the baseline measurements of the outcome variables as covariates. In order to test as secondary analyses whether the effect of magnesium oxide and magnesium sulfate on arterial stiffness are noninferior to the effect of magnesium citrate on arterial stiffness, a noninferiority margin (Δ) of 0.5 m/s is chosen based on the effect size of magnesium citrate on arterial stiffness found in previous research [9]. A one-factor ANCOVA, with use of the baseline measurements of the outcome variables as covariates, will be conducted to evaluate differences in responses between magnesium and placebo treatments. To prove noninferiority, the lower limit of the confidence interval of the difference between magnesium sulfate and magnesium citrate and the difference between magnesium oxide and magnesium citrate must not exceed the limit of Δ to be 95% sure that magnesium oxide and magnesium sulfate are not worse than magnesium citrate supplements by more than Δ. Treatment effects will be calculated at each time point (after 2, 12 and 24 weeks) with one-factor ANCOVA. Differences are considered statistically significant at *P* < 0.01 for the primary analyses (confirmatory) and *P* < 0.05 for the secondary analyses (exploratory). Statistical analyses will be performed using SPSS 23.0 software for Windows (SPSS Incorporated, Chicago, IL, USA). Normality of the residuals will be examined using the Shapiro–Wilk normality test. If a residual is not normally distributed, parameters will be log-transformed. If after log-transformation the residuals are still not normally distributed, nonparametric tests will be used. Missing data will not be replaced by estimates. Because of randomization, it is expected that confounders will be divided equally. Therefore, no adjustment for confounding will take place. The intention-to-treat principle will be applied in primary analyses. Secondly, we will conduct per-protocol analyses (exclude noncompliance subjects from the statistical analysis). To prove noninferiority, the confidence interval of the difference must exclude the margin in both the intention-to-treat and the per-protocol analyses. Finally, we will conduct subgroup analyses in which we will compare the effects of magnesium on arterial stiffness in subjects on antihypertensive therapy and subjects not on antihypertensive therapy. Because over time arterial stiffness may increase more rapidly in subjects treated for hypertension, our hypothesis is that magnesium may have a more pronounced effect on arterial stiffness in subjects on antihypertensive therapy.

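### The per-protocol set that must confirm noninferiority removes only noncompliant participants, so capsule-compliant users of non-study magnesium stay in it

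*Protocol article*

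**What the plan says.** All of this is in the Methods/design part of the protocol article.

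- **Per-protocol set (Statistical analysis):** "Secondly, we will conduct per-protocol analyses (exclude noncompliance subjects from the statistical analysis". No other reason for exclusion is named. The same section requires the confidence interval to exclude the 0.5 m/s margin in both the intention-to-treat and the per-protocol analysis.
- **Compliance (Compliance to the intervention):** "Subjects will be considered compliant when they take at least 80% of the capsules". The count comes from capsules returned at weeks 12 and 24. The section adds: "In addition, we will assess compliance by urinary magnesium concentrations at the end of the study". It gives no threshold and does not tie this measure to the analysis set.
- **Magnesium supplements (Characteristics of participants):** the list opens with "Participants who meet any of the following criteria are not eligible for this study" and includes "use of magnesium supplements or an investigational product within another biomedical within the previous 1 month". This is a look-back at entry. In that list only the blood-donation criterion is extended through the study period.
- **During the study (Interventions):** participants are asked to hold physical activity, food intake and alcohol steady. Medicines and supplements are not mentioned in that request. However, "subjects will record any signs of illness in diaries, as well as medication used, and any deviations from the protocol during the study".

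**The concern.** In a noninferiority comparison, anything that makes the arms more alike works in favour of the claim. Intention-to-treat is exposed to this, and that is why the plan asks the per-protocol analysis to agree. The second analysis protects only if it removes participants whose treatment was blurred.

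Here it removes people who took too few study capsules and keeps people who took additional magnesium. Someone on a weaker salt who also takes a commercial magnesium product may move towards the citrate response, yet counts as per protocol. Both analyses then carry the same dilution, and their agreement says little about it. At stake is a false conclusion that oxide or sulfate is no more than 0.5 m/s worse than citrate.

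The diaries collect medication and deviations, but the rule for the set does not use them.

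**Working it through.** **Tracing a participant through the rules.** Suppose a participant is eligible, begins a magnesium supplement at week 10 and takes 85% of capsules.

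1. Entry: passes, because the bar covers only the preceding month.
2. Capsule count: passes, because 85% exceeds 80%.
3. Urinary magnesium: there is no cut-off to fail. Extra magnesium would raise excretion and make the participant look more compliant.
4. Diary: the use may be recorded, but no stated rule acts on it.
5. Result: the participant is in the per-protocol set.

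**Reproducing the plan's sample size.** Inputs from Sample size calculation: margin 0.5 m/s, SD 0.9 m/s, probability 0.05, power 0.80. The true difference is taken as 0.

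- n per group = 2 × 0.9² × (1.645 + 0.842)² / 0.5² = 40.06, rounded up to 41. This matches the stated 41.
- A one-sided 0.025 would give 51, so the plan used one-sided 0.05. That level is used below.

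**False noninferiority under dilution.** Assume a true difference exactly at the margin, 41 evaluable per arm and an unchanged SD. Let off-protocol magnesium remove a fraction c of the difference, so the expected gap is d = 0.5 × (1 − c). One way this arises is a share c of the inferior arm being raised fully to the citrate response.

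- SE = 0.9 × √(2/41) = 0.199 m/s
- P(declare noninferior) = Φ((0.5 − d)/SE − 1.645)

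| c | d (m/s) | P(false noninferiority) |
|---|---|---|
| 0% | 0.500 | 5.0% |
| 5% | 0.475 | 6.4% |
| 10% | 0.450 | 8.2% |
| 20% | 0.400 | 12.7% |
| 30% | 0.350 | 18.7% |

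Each figure is for a single analysis. Requiring both analyses to pass cannot raise the probability above the smaller of the two. It lowers it little when both sets contain nearly the same diluted participants.

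**Power cost of removing users.** With a true difference of 0, power = Φ(0.5/SE − 1.645), where SE = 0.9 × √(2/n).

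| Removed per arm | n | Power |
|---|---|---|
| 0% | 41 | 81% |
| 5% | 39 | 79% |
| 10% | 37 | 77% |
| 20% | 33 | 73% |

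**The case against.** **The article condenses a fuller document.** A list of major deviations normally sits in the full protocol or SAP, and keeping diaries of deviations suggests such rules exist. This limits how much can be made of the point. But the article does not leave the set undefined: it states a rule, and the rule names noncompliance alone. If a wider definition exists, the two need to be aligned.

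**The dilution figures are a constructed case.** They place the truth at the margin and let extra magnesium close the gap fully for those who take it. Use that began mid-study would act for only part of follow-up. If extra magnesium simply added the same benefit in both arms, the gap would not shrink. This stands: the figures show sensitivity and do not predict the error rate.

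**Excluding people after randomization can itself bias.** This also stands, and it shapes the fix. If participants who fare badly were more often started on another drug, deleting them would remove poor responders from the inferior arm and favour noninferiority.

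**Stronger readings that the article does not support:**

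- A reader might extend the point to all the drug bars, including "use of lipid-lowering drugs and/or antihypertensive therapy that started in the past 6 months" and "use of proton pump inhibitors". The article gives no reason for these bars, and the direction of bias is not shown for them. Background reports that the earlier citrate trial lowered PWV without changing blood pressure, so a salt that is worse on PWV need not lead to more antihypertensive starts. Starts unrelated to arm would mainly add variance, which works against noninferiority.
- A reader might think the citrate–placebo result is affected. That primary analysis is intention-to-treat, so the per-protocol definition does not touch it, and dilution there would be conservative.
- A reader might fault the entry criterion for covering newly started drugs but not dose changes or stops. That is a preference about eligibility, not a contradiction, and randomization balances pre-baseline drift in expectation.

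**Conclusion.** The point holds for non-study magnesium. The stated per-protocol rule keeps capsule-compliant participants who take it, and neither the capsule count nor the urinary measure would remove them. The safeguard meant to back up intention-to-treat therefore shares this source of dilution.

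The size is unknown because the article gives no rate of supplement use. Under the assumptions in the working, losing 10% to 20% of a true 0.5 m/s difference takes false noninferiority from 5% to about 8% to 13%.

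The weight is moderate. Noninferiority is a secondary analysis that the article labels exploratory, although it is a stated aim and sets the size of the magnesium groups. The data needed are largely being collected, so the correction is nearly free if made before unblinding.

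**What to change.** Before unblinding, replace the parenthesis in Statistical analysis with an explicit definition: the per-protocol set comprises participants who took at least 80% of capsules and have no diary-recorded use of non-study magnesium between baseline and week 24. Diary entries should be classified blind to allocation.

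Do not automatically exclude participants with diary-recorded on-study changes in antihypertensive, lipid-lowering or proton pump inhibitor use. Report the noninferiority comparisons with and without them as a sensitivity analysis, together with their number per arm. Leave intention-to-treat and the primary citrate–placebo analysis as they are.

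**Cost:** two or three sentences, and no change to eligibility or participants' care. The per-protocol set becomes slightly smaller: removing 10% per arm (41 to 37) takes power from about 81% to about 77%. The rule is only as good as the diaries. Since the article does not bar supplements on study, it should be confirmed that the diary instructions ask for them by name. About 100 of the 162 had been included at submission, so this can still be made clear to the remaining 62 or so.

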### Sample size calculation

The current study is powered on arterial stiffness, the primary endpoint. The required sample size for noninferiority testing is calculated based on a margin of 0.5 m/s, a probability of 0.05 and a power of 0.80. Therefore, 41 subjects per magnesium group are needed. To compare magnesium citrate with placebo, we assume that the number of subjects per group calculated for a two-arm trial (*n* = 24) is sufficient. Because a 10% dropout rate is expected, 162 will be recruited to start the study. By taking into account that only 50% of the subjects included in the screening will meet all inclusion criteria and are willing to participate, 324 subjects are expected to participate in the screening visits.

This sample size calculation is based on an intra-subject variability of 0.9 m/s and a 1.0 m/s change in the PWV_c–f_ after 24 weeks of magnesium supplementation found in our previous study [9]. The equivalence margin of 0.5 m/s is based on the observed effect [9], which is 50% of the magnesium citrate supplementation effect compared to placebo. For the calculation of the sample size, the formula of Julious [21] was used.

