
## Discussion

The current study aims to replicate the effect of magnesium citrate on arterial stiffness that we found in our previous study [9], now with a slightly higher dose and to evaluate whether magnesium oxide and magnesium sulfate are noninferior to the effect of magnesium citrate in terms of arterial stiffness. We furthermore aim to unravel possible underlying mechanisms, including changes in blood pressure and gut microbiota diversity. To our knowledge, this is the first clinical trial that compares the long-term effects of different commercially available magnesium supplements on well-established cardiovascular risk markers, including arterial stiffness, blood pressure and gut microbiota [27–29]. Results of longitudinal epidemiologic studies have found that a decrease of 1.0 m/s in arterial stiffness, measured by the PWV_c–f_, corresponded to a reduced risk of cardiovascular events of 14% [30], underlining the potential clinical relevance of magnesium supplementation in the prevention of cardiovascular disease.

So far, only three studies have addressed the effect of magnesium supplementation on arterial stiffness [9, 31, 32]. Cunha *et al*. [31] reported an effect on blood pressure and endothelial function in hypertensive women after magnesium supplementation. However, no effect on arterial stiffness was found. Furthermore, the study by Cosaro *et al.* [32] showed neither an effect on blood pressure nor on arterial stiffness. Of note, the magnesium formulation, total daily dose, trial duration and study design were different between these studies. No studies have performed a head-to-head comparison between various magnesium formulations. Particularly, the difference between organic and inorganic formulations may be of interest.

It has been suggested that organic magnesium formulations (e.g. magnesium citrate) are superior to inorganic magnesium formulations, such as magnesium oxide, in terms of bioavailability [33, 34]. However, a meta-analysis of 34 clinical trials demonstrated that individuals supplemented with inorganic compounds, mainly with chloride as the counterbalancing anion, showed higher serum magnesium levels and more pronounced blood pressure reduction compared to organic compounds [35]. A total daily dose of 450 mg was chosen, because previous clinical trials showed a greater blood pressure-lowering response when the total daily dose of magnesium was increased [35].

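### Noninferiority to citrate can be declared without citrate having beaten placebo in this trial, so the claim may say nothing about whether oxide or sulfate works

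*Protocol article*

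**What the plan says.** All references are to the protocol article.

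- **Statistical analysis, decision rule.** The interval for oxide minus citrate, and for sulfate minus citrate, is compared with a margin of 0.5 m/s. The section then adds: "To prove noninferiority, the confidence interval of the difference must exclude the margin in both the intention-to-treat and the per-protocol analyses". No other condition is attached.
- **Statistical analysis, ranking.** Citrate versus placebo is the primary, confirmatory test at P<0.01. Noninferiority is a secondary analysis, and secondary analyses are labelled exploratory at P<0.05. An ANCOVA comparing magnesium with placebo is also planned. Its result is not tied to the noninferiority conclusion.
- **Sample size calculation.** The margin comes from the effect in the earlier trial, "which is 50% of the magnesium citrate supplementation effect compared to placebo". The group size rests on "a margin of 0.5 m/s, a probability of 0.05 and a power of 0.80", and the conclusion is: "Therefore, 41 subjects per magnesium group are needed".
- **Background.** The primary aim is to replicate the earlier citrate result. That result is given as 8.3 versus 9.1 m/s at a daily dose of 350 mg; the present dose is 450 mg.
- **Discussion.** Three earlier studies are named: the group's own and two that found no effect on arterial stiffness. One of those two "showed neither an effect on blood pressure nor on arterial stiffness". The authors note that these studies differed in formulation, dose, duration and design.

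**The concern.** A margin defined as half of the comparator's effect over placebo has meaning only if the comparator has that effect in the trial at hand. Here that is the open question: it is the primary hypothesis, it rests on one earlier trial, and the Discussion reports two trials without an effect on stiffness.

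The sample size assumes zero true difference between the salts. Zero difference also holds when no salt does anything. The design therefore has about the same chance of meeting the noninferiority criterion whether all salts work equally well or none works. The trial has the placebo arm needed to tell these two situations apart, but the rule does not use it.

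At stake is the question behind the secondary aim: whether other magnesium compounds share the effect attributed to citrate. When citrate fails against placebo, the rule still permits a noninferiority statement that cannot answer it.

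**Working it through.** **Inputs from the Sample size calculation section.** Margin Δ = 0.5 m/s, probability 0.05, power 0.80, SD 0.9 m/s, citrate effect 1.0 m/s, 41 per magnesium group, and 24 per group for citrate versus placebo. Arm sizes of 41/41/41/24 are inferred: 3 × 41 + 24 = 147, and 147 × 1.10 = 161.7, which matches the 162 to be recruited.

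**Step 1: reproduce the 41.** With zero true difference, n per group = 2 × SD² × (z₁₋α + z₀.₈₀)² / Δ².

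- One-sided 5%: 2 × 0.81 × (1.645 + 0.842)² / 0.25 = 40.06, so 41, as stated.
- One-sided 2.5% (two-sided 95% interval): 2 × 0.81 × (1.960 + 0.842)² / 0.25 = 50.86, so 51.

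The stated n fits one-sided 5%. The text does not give the level of the interval, so both levels are carried forward.

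**Step 2: one comparison when no salt works.** SE = 0.9 × √(2/41) = 0.199, and Δ/SE = 2.515. The chance of meeting the criterion is Φ(Δ/SE − z):

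- One-sided 5%: Φ(2.515 − 1.645) = 0.81.
- Two-sided 95% interval: Φ(2.515 − 1.960) = 0.71.

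**Step 3: both comparisons and the primary test together.** The trial was simulated with normal responses, SD 0.9, arms of 41/41/41/24, pooled variance, a shared citrate arm, all true effects zero and 40,000 runs. Noninferiority was judged on the clinically adverse side (higher PWV); by symmetry, reversing the sign gives the same null rate. Success for citrate means P<0.01 in the favourable direction. The per-protocol rows assume that 10% or 20% of each arm is excluded at random.

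| Rule applied | Interval | At least one salt noninferior | Same, and citrate fails |
|---|---|---|---|
| One analysis set | one-sided 5% | 91% | 91% |
| One analysis set | two-sided 95% | 84% | 84% |
| ITT and per-protocol, 10% excluded | one-sided 5% | 88% | 87% |
| ITT and per-protocol, 20% excluded | one-sided 5% | 84% | 84% |
| ITT and per-protocol, 10% excluded | two-sided 95% | 79% | 79% |
| ITT and per-protocol, 20% excluded | two-sided 95% | 74% | 74% |

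Citrate fails its own test in about 99.5% of these trials, so the last two columns barely differ.

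**Step 4: sensitivity to the SD (one analysis set).** With an assumed SD of 0.7, the chance of at least one claim is 99% (one-sided 5%) or 96% (two-sided 95%). With an assumed SD of 1.3 it is 70% or 57%.

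**Step 5: effect of requiring citrate to beat placebo first.** In the all-equal case, a noninferiority claim survives in about 0.3% (one-sided 5%) or 0.2% (two-sided 95%) of trials. If all three salts lower PWV by 1.0 m/s, the chance of at least one claim falls from about 92% to 87% (one-sided 5%).

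**Step 6: how often the condition is met.** For 41 versus 24, SE = 0.9 × √(1/41 + 1/24) = 0.231. The two-sided 1% critical value on 63 degrees of freedom is 2.656. Noncentral t power:

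| True citrate effect | Effect/SE | Probability that P<0.01 |
|---|---|---|
| 1.0 m/s (sample size assumption) | 4.32 | 95% |
| 0.8 m/s (9.1 − 8.3, Background) | 3.46 | 79% |
| 0.5 m/s (the margin) | 2.16 | 32% |

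**The case against.** **These rates are not error rates.** This stands. If all arms are equal, it is true that oxide is not worse than citrate by more than 0.5 m/s, and the 80% or so per comparison is simply the planned power. A reader might go further and infer that an all-ineffective trial would probably conclude that oxide or sulfate works. The documents do not support that. The rule claims only that a salt is not worse than citrate by more than the margin; the step to efficacy would be the reader's.

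**The plan already ranks the questions.** This stands in part. Citrate versus placebo is the confirmatory test, noninferiority is exploratory, and comparisons with placebo are planned, so a failed primary result would be visible beside any noninferiority claim. That softens the problem, but neither the label nor the extra ANCOVA enters the stated criterion.

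**Success is needed in both ITT and per-protocol sets.** This lowers the rates but does not protect. With all arms equal and random exclusions, both analyses centre on zero difference.

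**The contrary trials differed from this one.** The authors say so, and those trials do not show that citrate is ineffective. They do leave its effect open, as does the replication aim.

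**A condition may stand in a full protocol or SAP that is not shown.** Possible. But the article does not merely leave the matter out: it states what is sufficient to prove noninferiority, and this condition is absent.

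**Two noninferiority tests each use the full 5%.** A reader might want this counted as a fault. For analyses labelled exploratory, adjustment is largely a matter of preference, and no point is made of it here.

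**Conclusion.** The decision rule is badly fixed. As written, it allows noninferiority to citrate to be concluded when citrate has not been shown to differ from placebo, although the margin takes its meaning from that difference. If no salt works, at least one such conclusion is reached in about 84–91% of trials in a single analysis set, or about 74–88% with the per-protocol requirement. In nearly all of these trials citrate fails.

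The figures assume that 0.9 m/s is the SD of the compared responses, as the plan's own n of 41 requires, and that the arm sizes are 41/41/41/24. The ranges span the two readings of the interval level. The 10–20% exclusion and the SD range of 0.7–1.3 are assumptions, not figures from the article. At least one claim remains more likely than not in every scenario examined.

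The fault lies in what the noninferiority claim can mean, not in its truth or in a type I error rate. The primary analysis is unaffected. The point is worth correcting but does not threaten the trial's main conclusion.

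**What to change.** Add to the Statistical analysis section that noninferiority of oxide or sulfate will be concluded only if citrate is superior to placebo at week 24 in the primary test (P<0.01). If it is not, report the salt-minus-citrate differences with their confidence intervals descriptively, next to each salt's comparison with placebo, and make no noninferiority claim. No adjustment across the two salts and no separate superiority requirement for each salt is needed for this purpose.

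The change needs wording only: the placebo arm and the comparisons exist, and no subjects are added. The statistical cost depends on citrate's true effect. The condition is met with about 95% probability at 1.0 m/s, 79% at 0.8 m/s and 32% at 0.5 m/s. With a smaller true effect, some noninferiority claims would therefore be lost even though citrate works, because this trial had not shown it. The sponsor should accept that knowingly.
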